### Sample size

The primary outcome measure, the AQ, has been used for the power calculations. In previous RCTs using the AQ as an outcome measure, effect sizes of 0.79–1.42 [14, 15] were demonstrated. However, as the present intervention will use low-end cardboard VR goggles instead of expensive head-mounted displays, the current study uses a more conservative estimate for the post-treatment effect on the AQ. In order to detect a difference between the experimental and the waitlist control condition with a standardized effect size (Cohen’s d) of 0.50 (two-sided), an alpha of 0.05 and statistical power (1 − *β*) of 0.80, we need 64 participants in each condition (128 participants in total). With an anticipated dropout of 40%, this requires a total target sample size of 180 participants.

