### Randomization, blinding, and treatment allocation

A randomization list will be created with Random Allocation Software using block randomization of 6, 8, 10, and 12 blocks at an allocation ratio 1:1. Participants will be randomized into two groups: experimental or waitlist condition. The randomization list is kept by an independent researcher. This person reveals the next randomization outcome after every inclusion and thus ensures that the researchers are blind for treatment allocation. Due to the nature of the study, it is not possible to blind the participants for the randomization outcome.

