### Analyses

#### Statistical analyses

The primary outcome measure (AQ; [28]) and secondary study parameters (ATHQ, PHQ, IPQ, SUS, BAI, and Pearlin Mastery Scale) will be treated as continuous outcomes. Continuous variables will be presented as mean, standard deviation, and minimum and maximum number of observations. Categorical variables will be presented in terms of frequencies and percentages. Descriptive statistics of demographics and clinical outcomes will be compared between the experimental and the waitlist condition.

To assess whether attrition is non-random, we will construct a balancing table for background characteristics, pre-scores and other covariates in which participants with and without missing outcome observations are compared. Potential implications of non-random sample attrition on the observed treatment estimates will then be assessed by estimating treatment effect bounds for samples with non-random sample selection/attrition as proposed by Lee [47]. Using this approach we are able to infer whether observed differences between the intervention and control groups can be explained by extreme, non-random sample selection. Depending on these results, missing outcome observations for participants will be imputed based on pre-scores and a set of background characteristics. The quantitative analysis of the primary and secondary endpoints will be performed on an intention-to-treat (ITT) basis following the per-protocol analysis. The primary analysis will be based on ITT. Potential dependency between outcome measures is addressed using multivariate analyses. Potential heterogeneity will be addressed by estimating treatment effects for subgroups (e.g., based on pre-scores). In order to understand the mechanisms by which observed differences are generated, a rich set of analyses is performed based on variation in (1) experiences when using the app (e.g., perceived user friendliness, ecological momentary assessment, cybersickness, VR vs 360°) and (2) intensity of using the app. Per-protocol analysis will be based on two groups: (1) those who returned the post-test and follow-up questionnaires (completers) and (2) those who completed 50% or more of the treatment modules and returned the questionnaires (adherent completers). Comparisons will be made between and within the groups before and after measurements.

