Intention-to-treat and per-protocol analysis will be used on continuous scales using regression estimation standardized effect sizes (Cohen’s *d*) and confidence intervals will be calculated. Usage data through the mobile app (anxiety level during VR exposure, time spent in VR, number of VR sessions completed) will be collected during the study to model missing data. SPSS version 21 will be used for the analyses. A *p* value < 0.05 will be considered to indicate statistical significance. All design, implementation, and reporting will be carried out in accordance with Consolidated Standards of Reporting Trials (CONSORT) and Standard Protocol Items: Recommendations for Interventional Trials (SPIRIT) guidelines (Additional file 1) [48–50].

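### The article does not say that the primary regression adjusts for baseline AQ, and estimating subgroup effects by pre-score does not test whether the effect varies

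*Protocol article*

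**What the plan says.** **Primary model.** Statistical analyses: "Intention-to-treat and per-protocol analysis will be used on continuous scales using regression estimation standardized effect sizes", with confidence intervals. The section gives no covariate list and does not call the regression unadjusted.

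**Uses of pre-scores.** The same section gives baseline scores three roles: a table comparing participants with and without missing outcomes, imputation of missing outcomes (depending on the attrition results), and subgroups: "Potential heterogeneity will be addressed by estimating treatment effects for subgroups (e.g., based on pre-scores".

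**Before/after comparisons.** It also says "Comparisons will be made between and within the groups before and after measurements", without naming a method.

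**Sample size.** The calculation uses a post-treatment "standardized effect size (Cohen’s d) of 0.50 (two-sided", with 5% alpha and 80% power, and finds "we need 64 participants in each condition (128 participants in total". It adds: "With an anticipated dropout of 40%, this requires a total target sample size of 180 participants".

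**Availability of the covariate.** The Acrophobia questionnaire section has both AQ subscales taken at baseline and at post test. The ATHQ, BAI, PHQ-9 and mastery scale are also taken at both times.

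**The concern.** There are two issues, both about how baseline AQ is used.

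1. **The primary estimator is open.** Three analyses fit the text: post-test AQ compared by arm, change in AQ compared by arm, and post-test AQ by arm adjusted for baseline. They differ in precision. The first leaves chance baseline imbalance in the estimate, and the second can be less precise than ignoring baseline. If the choice is not fixed beforehand, it could be made after the data are seen.

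2. **The stated route to heterogeneity does not answer the question.** An effect estimated within each subgroup says whether that subgroup benefits. It does not say whether subgroups benefit differently. With p < 0.05 as the only threshold given, a significant result in one pre-score group and not in another is easily read as showing that the app works only in severe, or only in mild, cases.

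**Working it through.** **Inputs from the article:** d = 0.50, two-sided alpha 0.05, power 0.80, 64 per arm, 40% dropout, 180 randomized (Sample size); "at an allocation ratio 1:1" (Randomization, blinding, and treatment allocation), so 90 per arm.

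**Assumed, not in the article:** the correlation r between baseline and post-test AQ, shown over a range, with equal SD at the two times for the change-score figures; a split into two equal pre-score halves; and a significant/not significant reading of each half.

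**Step 1. Reproduce the plan's figure.** A two-sample t-test with d = 0.5 needs 63.8, so 64 per arm, and power at 64 is 80.1%. The stated 64 per arm (128) is right for an unadjusted comparison.

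**Step 2. Numbers left at the anticipated dropout.** 90 × (1 − 0.40) = 54 per arm. Unadjusted power at 54 is 73.1%. (128/0.60 = 213.3, so 214 would be needed; 128 × 1.4 = 179.2 accounts for 180. That shortfall is a separate point, and 54 per arm serves here only as the working sample size.)

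**Step 3. Power under the three readings, 54 per arm, d = 0.5.**
- Adjusted for baseline: residual SD is multiplied by √(1 − r²), so the effective effect is 0.5/√(1 − r²).
- Change score: SD is multiplied by √(2 − 2r), so the effective effect is 0.5/√(2 − 2r).

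| r (assumed) | Post-test only | Change score | Baseline-adjusted |
|---|---|---|---|
| 0.2 | 73% | 53% | 75% |
| 0.3 | 73% | 59% | 77% |
| 0.4 | 73% | 65% | 80% |
| 0.5 | 73% | 73% | 84% |
| 0.6 | 73% | 82% | 90% |

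Worked example at r = 0.4: √(1 − 0.16) = 0.917, 0.5/0.917 = 0.546, and power at 54 per arm is 80.2%.

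Break-even: 54 adjusted participants per arm match 64 unadjusted when 1 − r² = 54/64, so r = √(1 − 0.84375) = 0.395.

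**Step 4. Subgroups.** Two equal halves of 54 per arm give 27 per arm each. With the same true d = 0.5 in both, each test has power 0.438. The chance that exactly one is significant is 2 × 0.438 × (1 − 0.438) = 0.492, or 49%. The result depends little on dropout: 32 per arm in each half gives 50%, and 45 per arm (no loss at all) gives 45%.

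**The case against.** **The regression may well be adjusted.** A reader might infer from the article that the primary analysis is unadjusted. The text does not support that. It is silent on covariates, refers to pre-scores as covariates when describing the attrition table, and a condensed article may leave the covariate list to a fuller document. Nor does reporting Cohen's d, or sizing the trial on an unadjusted difference, settle it, since both are common alongside an adjusted analysis. This objection stands, and the point is limited to asking that the model be stated.

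**Baseline is not ignored.** A reader might also infer that pre-scores serve only imputation and subgroups. That is wrong: they also enter the attrition table, and before/after comparisons are planned. None of these, however, states that the treatment effect is adjusted for baseline.

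**Adjustment may not bring power to 80%.** This also stands. It does so only if r is about 0.40 or more. The article gives no r, and the AQ-Anxiety entry cut-off of 45.45 narrows the baseline range and may lower it. The shortfall itself comes from the dropout inflation, not from the choice of model.

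**The subgroup rule may be read too harshly.** The article specifies no median split and no comparison of p-values, does not exclude an interaction, and this is not the primary analysis. The 49% is therefore illustrative. But the article does name a method for heterogeneity, and that method as stated involves no test of a difference between subgroups.

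**Conclusion.** The point holds as a request to specify, with two parts.

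- **Baseline adjustment.** The article leaves open whether baseline AQ is in the primary model. Among the three readings that fit the text, the adjusted one is the most powerful at every r tabulated. Its gain over post-test only at 54 per arm is small at r = 0.2 (73% to 75%) and substantial at r = 0.5 (73% to 84%). The gain over a change score is larger when r is low. These figures rest on d = 0.5, 40% loss and an assumed r. They do not show that adjustment would make good the sample-size shortfall.

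- **Heterogeneity.** Estimating effects by pre-score subgroup does not test whether effects differ. Under the assumed equal split and p < 0.05 reading, identical effects give discordant halves in about 49% of trials.

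Both are worth changing because the remedy is cheap, but neither shows that the planned primary analysis is invalid.

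**What to change.** 1. State the primary model: linear regression of post-test AQ on arm plus baseline AQ, intention-to-treat, reporting the adjusted mean difference with its 95% CI. Cohen's d can be given alongside.
2. Use the same form for ATHQ, BAI, PHQ-9 and mastery, each with its own baseline. State that the before/after comparisons do not replace this model.
3. Assess heterogeneity by adding one treatment × continuous baseline-AQ interaction to the primary model. Report any subgroup estimates only as description beside it.

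The cost is a few sentences in the analysis section, or a pointer to a fuller document if the model is already fixed there. No extra participants, visits or data are needed, since the baseline scores are already collected. Because recruitment had started by the time of submission, the wording should be settled and dated before outcome data are examined.

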### Data monitoring and management

All data will be collected at the Section Clinical Psychology of VU University of Amsterdam by a staff member and handled confidentially. The data (baseline, AQ after module 6, post test, and follow-up data) will be captured electronically in a secured online survey platform [46]. Through the 0Phobia app the following data is collected: anxiety level during VR exposure, time spent in VR, number of VR sessions completed, and information from three exercises (setting goals for the intervention, evaluating anxiety provoking thoughts and creating a personal fear hierarchy). The data will be coded which serves as a trial identifier consisting of four numbers and captured electronically in a secured online database, which is hosted on a server of our university. No personal identification data will be collected through the app. The data will be uploaded into the IBM SPSS database. Data from the different measurements will be kept in separate databases and merged into a master database only after data collection is completed and each individual database is locked. Data will be coded and the key connecting names to numbers will be kept in a separate, secure location in the principal investigator’s office. The data will be anonymized but linked with the trial identifier consisting of four numbers. Coded data will be electronically stored at the VU Amsterdam, separate from identifying information. Access will be password protected. Only the principal investigators and trial researchers will have access to the final dataset. All collected data will be used only for the purposes of this research. The project group will analyze the data, and both positive and negative trial results will be disclosed. The publication policy is in agreement with the publication statement of the CCMO (see: http://www.ccmo.nl). A data monitoring committee is not required by the Ethics Committee because of the low impact on the safety of the participants. No interim analysis is anticipated as this is not required for a trial of this type.

### Harms

Previous studies in similar samples have shown that studies with VRET can be carried out safely, without a significant risk for unwanted effects (e.g., [18, 27, 32, 51]).The VR exposure environment uses gradual exposure which means that subjects start with relatively easy levels of height situations which induce a small amount of fear. When this situation becomes less fearful, they move on to the next level. In this way, fear levels are manageable. It is, nevertheless, possible that participants may get distressed, cybersick, or feel that they will lose their balance and fall during the intervention. In these cases, participants are instructed to remove their VR goggles. By removing them, feelings of distress, cybersickness or imbalance are immediately reduced. Furthermore, participants may experience distress while completing questionnaires when asked about mental health symptoms. However, administering these instruments is crucial to draw conclusions about the feasibility and efficacy of the intervention. In case of an undesirable emotional reaction both during the intervention as well as during the follow-up assessments, the research assistant and at least one experienced clinician (the principal investigator) can be contacted by the participant and will be available to provide support if necessary or desirable. Participants can always discontinue the intervention without providing any reasons.

### Protocol amendments and publication

If necessary, protocol amendments will be submitted to the Ethics Committee and specified in the trial registry. There are no restrictions on reporting findings of this trial. Findings will be published in peer-reviewed journals.

## Discussion

The aim of this study is to evaluate effectiveness and user-friendliness of a self-guided VRET for acrophobia delivered through a smartphone app using cardboard VR goggles. Due to high treatment costs, long waiting lists, lack of health insurance coverage in the Netherlands, and a general reluctance to seek treatment, access to evidence-based therapy is currently limited. Given the psychological burden that phobias carry, the increased risk of developing comorbid depressive and anxiety disorders [8], and the heavy economic burden for society [9], there is a strong need for affordable and scalable self-guided interventions. Recent research into mobile apps as a method for treating psychiatric disorders are promising (e.g., [23, 52, 53]) and research into VRET as a treatment technique for specific phobias has shown positive results (see [13] for a review). The combination of a mobile app with affordable VR goggles is an innovative and promising scalable solution to deliver clinically validated mental health care for people suffering from specific phobias such as acrophobia. Advantages of an app-based VRET are lower costs, no waiting lists, better accessibility and participant retention, real-time progress monitoring, portability, and flexibility. Using a gamified exposure application, subjects may be more engaged and less distressed compared to traditional exposure therapy. Game elements may reduce distress as compared with traditional exposure therapy [20]. With the possibility of playing the gamified VR contact repeatedly, continues confrontation of phobic stimuli may be facilitated [21].

In sum, the current study will assess the efficacy and user-friendliness of 0Phobia, a mobile-app-based gamified VR treatment for acrophobia, in a RCT. This study will add to the development of innovative and scalable delivery methods of evidence-based treatments.

### Trial status

Recruitment started March 2017 and is ongoing at the time of initial manuscript submission (June 2017).

## Abbreviations

ANOVA: Analysis of variance
AQ: Acrophobia Questionnaire
ATHQ: Attitudes Towards Heights Questionnaire
BAI: Beck Anxiety Inventory
CBT: Cognitive behaviour therapy
GLM: Generalized linear models
IPQ: Igroup Presence Questionnaire
PHQ: Patient Health Questionnaire
RCT: Randomized controlled trial
SPSS: Statistical Package of Social Science
SUS: System Usability Scale
VR: Virtual reality
VRET: Virtual reality exposure therapy
VU: VU University Amsterdam
WSQ: Web Screening Questionnaire
